### Intervention

This study will be performed in the UK across 15 participating centres starting 1 August 2018 and with the aim to complete recruitment by 31 October 2019. Consenting participants will be observed for 10 weeks following creation of their AVF and will undergo Doppler US scans during weeks 2, 4, 6 and 10. Routine clinical examination will be undertaken as per local policy with a final clinical examination at week 10 to evaluate the fistula.

### Doppler US surveillance

Duplex Doppler US machines used for the study must have B-mode imaging frequencies of at least 7 MHz. The machines will have both high (>12 MHz), midrange (>7 MHz) and curvilinear (approximately 3 MHz) probes. Scans will be carried out by vascular scientists, surgeons, sonographers and other personnel trained in arteriovenous fistula surveillance by Doppler US; training days have been provided to ensure a standardised approach. The parameters measured for the study will be recorded on an agreed study proforma and include: brachial artery (or subclavian/axillary artery in the presence of a high bifurcation) flow volume and resistance index, outflow vein diameter, anastomotic diameter, AVF depth, presence of a flow limiting stenosis and fistula thrombosis.

### Definitions used within study

#### Primary patency

The interval between access creation to thrombosis event or first surgical/radiological intervention.

#### Secondary patency

The interval between access creation to abandonment of the access including all radiological and surgical salvage procedures in between.

#### Clinical maturation

Suitability to cannulate based on clinical examination.

#### Functional maturation

Ability for the access to achieve adequate dialysis.

### Inclusion criteria

Aged 16 years or older.Can provide fully informed consent.Have ESRD and require haemodialysis or are likely to do so imminently.Are due creation of a wrist or elbow AVF, including the following types of fistula with a minimal acceptable threshold of 2 mm venous diameter (with a tourniquet applied) at the site chosen:Radiocephalic.Ulnobasilic.Brachiocephalic.Brachiobasilic.

### Exclusion criteria

Attempted formation of proximal neoanastomosis at the forearm cephalic and basilic venous systems following failure of a standard radiocephalic or ulnobasilic fistula.Known central venous stenosis (including those who undergo simultaneous central venous angioplasty/stenting and AVF creation).Anticipated that it will not be possible to perform serial US scanning.

### Primary outcome measure

Primary fistula patency at week 10, according to surrogate US parameters. This is assessed using venous diameter and blood flow measurements:Wrist fistula considered to be patent if there is a minimum venous diameter of 4 mm with a blood flow measurement of >400 mL/min.Elbow fistula, considered to be patent if there is a minimum venous fistula diameter of 5 mm, with a blood flow measurement of >500 mL/min.

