### Secondary outcome measures

For those patients established on dialysis, successful use of the fistula, determined by its use for dialysis on 3 separate occasions during the 10 weeks after the AVF surgical creation.Clinical suitability for dialysis based on examination alone according to local practice, assessed 10 weeks after AVF surgical creation.Formation of a new fistula (including fashioning of proximal neoanastomosis) or radiological salvage procedure, measured by collecting the number and type of these interventions during the 10 weeks after AVF surgical creation.Fistula thrombosis rate: the number of fistulae that thrombose during the 10 weeks after surgical creation.Secondary fistula patency rate: measured by the time interval (in days) between AVF creation until abandonment of the AVF, including all radiological and surgical salvage procedures in between, during the 10 weeks after AVF surgical creation.Patient acceptability based on the proportion of patients that complete their study US scans 10 weeks after AVF surgical creation.

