### Blinding

Both the patient and the treating clinical team will be blinded to the results of the Doppler US.

The only acceptable reasons for unblinding are:The participating centre’s local standard of care requires a scan, or a clinical need for a scan is identified, in which case the centre will have access to study scan data for that time point (but not the other study scans) to avoid unnecessary additional scans being scheduled, or:During a trial scan, the AVF is seen to be thrombosed, in which case this information would be shared with the clinical care team to enable appropriate care to continue. In such cases, no further study scans would be required. Clinical outcome data will still be collected at week 10.

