#### Analysis of primary and secondary outcomes

The primary fistula patency rate at week 10 will be calculated alongside an exact 95% CI based on all participants enrolled. It will also be calculated based on participants whose fistulas did not fail early. Patency will be assessed using the results from each US scan up to week 10.

The secondary outcomes will be presented using descriptive summary statistics.

Mixed multivariable logistic regression will be used to model primary fistula patency by 10 weeks, which will then be used as a risk-score calculator in the phase II trial. Two models will be built, one for wrist fistulas and one for elbow fistulas. Measurements taken from the first scan performed at week 2 will be considered as parameters in the model initially, and further parameters from either the second scan or the third scan will then be considered. The choice of second or third scan will be based on the best fitting parameters, as assessed by significance level. A random effect for the participant will be included in the models to account for multiple scan data per participant. The aim will be to build parsimonious models, which contain the minimum number of measurements required to effectively predict primary fistula patency. A receiver operating characteristic curve analysis of the developed risk scores will be used to assist decisions regarding an appropriate cut-off for an indicator for when intervention is required for both wrist and elbow fistulas. The PPV will be calculated alongside an exact 95% CI for the chosen risk score cut-off.

It is anticipated that some participants will not attend all scans, and therefore, some scan data will be missing. Levels of missing data will be summarised for each of the scan time points and will be considered when choosing which scan results to use in the final model. Any missing primary and secondary outcome data will not be imputed. Missing data for parameters in the modelling of primary fistula patency will be imputed using multiple imputation if the level of missing data is greater than 10%.

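### Primary patency is defined in two incompatible ways, so the classification of salvaged and of event-free sub-threshold fistulas, and with it the primary rate and the PPV, is not fixed

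*Protocol article*

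**What the plan says.** All references are to the Protocol article.

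- *Definitions used within study, Primary patency*: "The interval between access creation to thrombosis event or first surgical/radiological intervention". This is a time-to-event definition with no ultrasound threshold.
- *Primary outcome measure*: "Primary fistula patency at week 10, according to surrogate US parameters". A wrist fistula is patent with a "minimum venous diameter of 4 mm with a blood flow measurement of >400 mL/min"; the elbow thresholds are 5 mm and more than 500 mL/min. Prior intervention is not mentioned.
- *Blinding*: once a study scan shows thrombosis the clinical team is told, and "In such cases, no further study scans would be required". Clinical outcome data are still collected at week 10.
- *Analysis of primary and secondary outcomes* sets the main estimate as follows: "The primary fistula patency rate at week 10 will be calculated alongside an exact 95% CI based on all participants enrolled". A second rate is restricted to fistulas without early failure. The section adds "Patency will be assessed using the results from each US scan up to week 10" and "Any missing primary and secondary outcome data will not be imputed".
- *Sample size*: PPV 72% with a half-width of 10 points, 78 predicted failures, 312 fistulas, and 347 recruited to allow for 10% dropout.

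**The concern.** One term carries two meanings, and they disagree on fistulas the study expects to see. Salvage within the 10 weeks is counted as a secondary outcome, a scan may be unblinded on clinical need, and the *Consent* section leaves clinicians free to treat. Some fistulas will therefore be salvaged and then measured at week 10.

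Three results depend on how those fistulas are scored: the primary patency rate, the event modelled by the logistic regression, and the PPV of the resulting risk score. The PPV matters most. Phase I exists to show that ultrasound picks out at-risk fistulas. If a fistula is flagged early, salvaged and then passes at week 10, the event definition calls the flag right and the ultrasound definition calls it wrong.

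A second, smaller gap concerns thrombosis. The primary outcome asks for week-10 diameter and flow, and a fistula found thrombosed at an earlier study scan has no further scans. The scoring of that fistula is left to inference.

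**Working it through.** **1. The two definitions compared**

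| Fistula by week 10 | Event definition (*Primary patency*) | Ultrasound definition (*Primary outcome measure*) |
|---|---|---|
| No event, meets thresholds | patent | patent |
| Salvaged, then meets thresholds | **not patent** | **patent** |
| No event, below thresholds | **patent** | **not patent** |
| Salvaged, below thresholds | not patent | not patent |
| Thrombosed at an earlier scan, no week-10 scan | not patent | no week-10 measurements; not stated |

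Rows 2 and 3 are direct contradictions. Row 5 is a missing statement.

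**2. The plan's own sample size**

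- n = 1.96² × 0.72 × 0.28 / 0.10² = 77.44, rounded up to 78.
- 78 / 0.25 = 312.
- 312 / 0.90 = 346.7, rounded up to 347.

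All three figures reproduce. The sample size is not in dispute.

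**3. Effect on the PPV (illustration)**

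Take 78 predicted failures, of which 56 are true under the event definition: 56/78 = 71.8%. Assume 8 of the 56 were salvaged and met the thresholds at week 10. Under the ultrasound definition they become false positives: 48/78 = 61.5%. The difference is 8/78 = 10.3 points, against a planned half-width of 10. Eight fistulas are 8/312 = 2.6% of the evaluable cohort. The figure 8 is an assumption. Flagged, event-free fistulas below the thresholds (row 3) move the PPV the other way, so the net effect is unknown.

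**4. Effect on the patency rate (illustration)**

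Use 312 fistulas and the plan's 20% failure: 62 failures, 250 patent on ultrasound, 250/312 = 80.1% (exact 95% CI 75.3% to 84.4%). Let S be the number salvaged that still pass at week 10.

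| Assumed share | S | Ultrasound definition | Both conditions required, (250 − S)/312 |
|---|---|---|---|
| 2% | 6 | 80.1% | 78.2% |
| 5% | 16 | 80.1% | 75.0% |
| 10% | 31 | 80.1% | 70.2% |

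The last column equals the event definition only if every fistula below the thresholds also had an event. If U of the 62 were event-free, the event definition gives (250 − S + U)/312. At S = 16 this runs from 234/312 = 75.0% (U = 0) to 296/312 = 94.9% (U = 62, an extreme). The two definitions can therefore differ in either direction.

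**5. Missing outcomes**

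The rate is based on everyone enrolled, yet missing outcomes are not imputed and 347 − 312 = 35 dropouts are planned for. The text does not say how a participant with no event and no week-10 scan enters that rate.

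**The case against.** The strongest reply is that the definitions can be read together. The section on when surveillance should be performed equates primary with unassisted patency, so the no-intervention condition may carry over into the primary outcome with the thresholds added. The ultrasound surrogate is openly acknowledged among the study's limitations, and detailed scoring rules may sit in an analysis plan that is not shown. The combined reading is sensible and is essentially the fix below. But the primary outcome says what makes a fistula patent and names only diameter and flow. An analyst following that section would count a salvaged fistula as patent. An analysis plan could settle the scoring, but the protocol would still contradict itself.

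On thrombosis, a reader might infer that certain failures drop out of the analysis as missing. The document does not support that. Thrombosis is a recorded scan parameter under *Doppler US surveillance*, so seeing it is an observed result. Clinical outcomes are still collected at week 10. The *Analysis plan* keeps fistulas that failed in the first 2 weeks, and the second rate, which excludes early failures, makes sense only if they count as failures in the main rate. Figures such as 87% to 91% patency (thrombosed fistulas dropped, assuming 8% to 12% thrombose) or 72% (250/347, dropouts scored as failures) each rest on a scoring rule the protocol does not state. They are not evidence of bias.

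A reader might also take "Patency will be assessed using the results from each US scan up to week 10" to mean that predictor measurements are mixed into the outcome. It can equally mean that a failure seen at an earlier scan counts toward the week-10 result. The wording needs tightening, but no error is shown.

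**Conclusion.** The contradiction is real and concerns the primary outcome, so it goes beyond detail that a protocol may leave to the analysis plan. It should be resolved before outcomes are analysed. Its size cannot be fixed from the document, which gives neither a salvage rate nor the share of event-free fistulas below the thresholds. If 2% to 10% of fistulas are salvaged and then pass, whether salvage counts as failure changes the patency rate by about 2 to 10 points. Eight such fistulas among the predicted failures would shift the PPV by its whole planned half-width. Both figures are illustrations under stated assumptions.

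The thrombosis and missing-data wording is a gap to close. It does not show that failures will be miscounted. A separate minor point is acceptability, "Patient acceptability based on the proportion of patients that complete their study US scans 10 weeks after AVF surgical creation": the text does not say whether scans cancelled after thrombosis count against completion.

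**What to change.** Use one definition in *Primary patency*, *Primary outcome measure* and *Analysis of primary and secondary outcomes*:

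- **Patent at week 10**: no thrombosis, abandonment, or surgical or radiological intervention before week 10, **and** the week-10 scan meets the thresholds for the site.
- **Not patent**: thrombosis, abandonment, new fistula or intervention before week 10, whether or not a week-10 scan exists; or a week-10 scan below the thresholds.
- **Missing**: only fistulas with no such event and no week-10 scan. State how they enter the rate on everyone enrolled, for example by reporting bounds with all missing counted as failed and all counted as patent. If all 35 planned dropouts were of this kind, the bounds would lie 35/347 = 10.1 points apart.
- **Earlier scans**: they contribute to the outcome only through failure events; their diameter and flow serve as predictors.

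The cost is wording. Thrombosis, salvage, new fistula formation and abandonment are already collected as secondary outcomes, and the sample size stays at 347. Because both conditions must be met, the patency rate among fistulas with a known outcome cannot exceed that under either definition alone, so the reported figure may be lower.

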### Consent

The rights of the patient to refuse to participate in the study without giving a reason will be respected. After the participant has entered into the study, the clinician remains free to treat the patient according to best standards of care, irrespective of their involvement in the study. The participant will remain within the study for the purposes of follow-up and for data analysis. Similarly, the participant will remain free to change their mind to participate at any time without giving a reason and without prejudicing his/her further treatment.

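### The primary outcome is named primary patency but scored on week-10 ultrasound alone, so a fistula salvaged before week 10 can count as a success

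*Protocol article*

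**What the plan says.** Under Definitions used within study, primary patency is "The interval between access creation to thrombosis event or first surgical/radiological intervention". The section on when surveillance should be performed uses the term in the same sense, equating primary with unassisted patency. The Introduction speaks separately of assisted primary patency.

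Under Primary outcome measure, the outcome is "Primary fistula patency at week 10, according to surrogate US parameters". The rule for the wrist is "Wrist fistula considered to be patent if there is a minimum venous diameter of 4 mm with a blood flow measurement of >400 mL/min". The rule for the elbow has the same form, with a 5 mm vein and "with a blood flow measurement of >500 mL/min". Neither rule mentions thrombosis or earlier intervention.

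Events before week 10 are foreseen. Secondary outcome measures covers new fistulas and radiological salvage, "measured by collecting the number and type of these interventions during the 10 weeks after AVF surgical creation", and thrombosis as "the number of fistulae that thrombose during the 10 weeks after surgical creation". Its secondary patency item adds abandonment and surgical salvage. Under Consent, "the clinician remains free to treat the patient according to best standards of care, irrespective of their involvement in the study".

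Analysis of primary and secondary outcomes takes the patency rate over everyone enrolled. It models the same outcome separately for wrist and elbow to obtain the phase II risk score, and calculates the PPV at the chosen cut-off. It also says: "Any missing primary and secondary outcome data will not be imputed".

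**The concern.** The definition and the outcome carry the same name but give opposite answers for a fistula that is salvaged during follow-up and then measures well at week 10. Under the definition its primary patency has ended. Under the outcome rule it is patent.

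Such fistulas are not a random subset. Care continues as usual, and salvage is likeliest where the fistula is failing, which is also where early ultrasound should raise a flag. If a flagged fistula is rescued by standard care and scored as patent, the flag counts as a false positive although it was right. The risk models would then be fitted to an outcome in which poor early measurements sometimes lead to success because of treatment. The effect runs against the tool under study. The article makes phase II conditional on ultrasound identifying at-risk fistulas, so the decision to proceed depends on this variable.

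**Working it through.** **1. The two rules side by side**

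| History up to week 10 | Definition of primary patency | Primary outcome rule |
|---|---|---|
| No event, meets cut-offs | patent | patent |
| Salvaged, then meets cut-offs | ended | **patent** |
| Salvaged, does not meet cut-offs | ended | not patent |
| No event, below cut-offs | patent | not patent (the disclosed surrogate) |
| Thrombosis, abandonment or replacement found clinically, no week-10 scan | ended | no explicit rule |

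The second row is the conflict. The fourth and fifth rows are taken up under the objection.

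**2. The plan's own figures (Sample size section)**

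Inputs: PPV 72%, precision ±10%, 25% of fistulas predicted to fail, 10% dropout.

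- Predicted failures: 1.96² × 0.72 × 0.28 / 0.10² = 77.4, rounded up to 78.
- Evaluable fistulas: 78 / 0.25 = 312.
- Recruited: 312 / 0.9 = 346.7, rounded up to 347.
- Per site, 78 / 2 = 39 predicted failures: exact 95% CI at 72% is 55.3% to 85.2%.

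All four match the article. The point does not touch them.

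**3. Illustration for the PPV**

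Assumption: 72% is the PPV when salvage counts as failure. True positives are then 0.72 × 78 = 56.2, taken as 56. Let k be the number of these that are salvaged and pass at week 10. The PPV under the ultrasound-only rule is (56 − k)/78.

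- k = 0: 56/78 = 71.8% (exact 95% CI 60.5% to 81.4%)
- k = 4: 52/78 = 66.7% (55.1% to 76.9%)
- k = 8: 48/78 = 61.5% (49.8% to 72.3%)

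**4. Illustration for the patency rate**

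Assumption: the article's 20% early failure is the failure rate with salvage counted as failure. Failures are then 0.20 × 312 = 62.4, taken as 62, so 250/312 = 80.1% are patent (exact 95% CI 75.3% to 84.4%, half-width about 4.6 points). The article gives no share of fistulas that are salvaged and then pass, so a range is shown:

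- 2% (6 fistulas): 256/312 = 82.1%
- 5% (16 fistulas): 266/312 = 85.3%
- 10% (31 fistulas): 281/312 = 90.1%

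The last value would need half of the 62 failures to be rescued and to pass within ten weeks. It is an outer bound and not an expectation.

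**The case against.** The strongest reply is that the two sections should be read together. The outcome is named with a term defined in the same Methods section. The cut-offs might then say only when a fistula is patent, leaving the definition to say when patency is still primary. On that reading a salvaged fistula already fails. This is plausible and may be what was meant, but no sentence states it, and anyone applying the cut-offs as printed would score the salvaged fistula as patent.

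A second reply is that the analysis plan, which is not shown, may settle the matter. That would be a fair answer to a missing detail. Here the protocol gives its primary outcome two incompatible meanings.

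The size is also open to challenge. Clinicians do not normally see the study scans, so salvage within ten weeks may be uncommon, and 8 of 78 is simply the number that moves the PPV by about the stated precision. This stands: the figures show sensitivity and are not estimates.

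A reader might infer two stronger points, which the article does not support:

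- **That recorded failures without a week-10 scan are left missing and drop out of the rate.** The no-imputation sentence does not say that a known thrombosis is a missing outcome. The Analysis plan section keeps all enrolled participants and expressly includes fistulas that failed in the first two weeks. The outcome analysis adds a separate rate without early failures and uses every scan up to week 10. Early failures and thromboses seen on a scan are therefore probably meant to count as not patent. What remains is that nothing is stated for a later event found clinically.
- **That failing an untouched fistula just below the cut-offs is a further contradiction.** This is the surrogate endpoint itself. The article names it as the main limitation and justifies it by the wish to keep predialysis patients in the study.

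**Conclusion.** The definition of primary patency and the primary outcome rule conflict on prior intervention and must be reconciled, because the patency rate, both risk models and the PPV all rest on this one variable. Applied as written, the outcome counts a salvaged fistula that meets the cut-offs as a success. This raises the patency rate and lowers the PPV.

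The direction follows from the text, given that salvage is concentrated in failing fistulas. The size cannot be derived, because the article gives neither a salvage rate nor a pass rate after salvage. Under the assumptions shown, as few as 4 affected cases cost the PPV about 5 points, and 8 cost about 10, which matches the precision the study was sized for. The scoring of clinically detected failures without a week-10 scan is a clarification and not an error. No stated sample size figure is wrong.

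**What to change.** Amend the primary outcome so that a fistula is primary patent at week 10 only if both conditions hold:

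- it meets the existing ultrasound cut-offs;
- it has had no thrombosis, abandonment, replacement or first surgical or radiological intervention before the week-10 scan.

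Use this variable for the patency rate, both risk models and the PPV. Report the ultrasound-only (assisted) version as a separate line.

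Add one clarifying sentence: any such recorded event counts as not patent whether or not a week-10 scan exists, and the no-imputation rule applies only where status is truly unknown.

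The cost is wording. The events already appear among the secondary outcomes, although it is worth checking that surgical salvage and event dates are recorded well enough to place each event before or after the scan. The reported patency rate may be lower. The figures of 78, 312 and 347 do not change.
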